### **Potential Use of Findings**

SMC is a new intervention approved by WHO as policy in the March 2012. The main and urgent objectives of the project are to identify the most effective method to deliver SMC, and to obtain more information on the longterm impact of SMC on malaria immunity. Mali is one of the countries supported by the US President's Malaria Initiative (PMI) implemented through USAID. The aim of PMI is to reduce malaria-related deaths by 50 percent in selected countries by achieving 85 percent coverage of proven preventive and curative interventions, in support of the National Malaria Control Program. Finding the optimal delivery method of the SMC will allow optimal deployment of the strategy through the country for higher impact on the mortality and mortality from malaria in Mali and contribute in achievement toward the millimun development goal and the PMI objectives. The project will also assess the effect of SMC on malaria immunity when given over three consecutive years, so that better understanding of the malaria immunity will be gained and appropriate measures could be taken to accompany the implementation of the strategy if needed

The project will be carried out through local health system. Staff of the health center in selected villages will be trained to carry out the SMC interventions with support of the project team composed of MRTCC, LMIV and the National Malaria Control Program. The project will collaborate with the President Malaria Initiative (PMI) of the USAID mission in Bamako. The MRTCC is currently assuring the training, monitoring and evaluation of US President Malaria Initiative (PMI) program to Mali funded through USAID and the collaboration will continue through this project.

## **3. Objectives & Outcome Measure(s)**

### **A. Study objectives**

#### ***Overall objective***

The overall objective is to identify the most effective method to deliver SMC, and to obtain more information on the long term impact of SMC on malaria immunity.

***Specific objectives***

1. To determine the optimal mode (fixed-point (FPD) vs door-to-door delivery (DDD); directly observed treatment (DOT) vs. non-DOT (NDOT)) and frequency (3 vs. 4 doses per season) of SMC delivery
2. To compare quantitative measures of immunity in children who do and do not receive SMC.
3. To monitor the impact of SMC on the molecular markers of the resistance of *P. falciparum* to SP and AQ.

**B. Study Outcome measure(s)**

The primary outcomes are:

1. SMC coverage for the determination of the optimal mode of delivery during Year 1. SMC coverage will be defined as proportion of the children who have received the three treatments doses at each of the three rounds of SMC.
2. Incidence of the clinical malaria for the optimal frequency of SMC in Year 2. Clinical malaria will be defined as signs and symptoms suggestive of malaria with positive RDT and/or positive blood smear.

Secondary trial outcomes of the study include:

1. Parasite prevalence defined as the proportion of children with a positive malaria blood smear and parasite density measured in Years 1, 2 and 3.
2. Prevalence of moderate anemia defined as hemoglobin concentration < 8 g/dL measured by hemoglobin analyzer.
3. Cellular and humoral antimalarial immune responses to malaria parasites.
4. Levels of cytokines and other host responses measured in sera/plasma or in immune cells.

5. Frequency of mutations at codons 51, 59, and 108 of the dhfr gene, 437 and 540 of the dhps gene, codon 76 in the *P. falciparum* chloroquine transporter gene (pfcr), and codon 86 of the *P. falciparum* multidrug resistance gene one (pfmdr1)

## 4. Study Design

### A. Detailed Description of Study Design

#### *Overall design*

The study will use a cluster randomized design over three years. Eight sub-districts will be randomly selected among the 13 sub-districts of Ouelessebouyou but excluding the sub district of the Ouelessebouyou where the IMEP cohort study is ongoing. These eight sub-districts will be randomized so that the intervention begins in four districts during the first year (Year 1), in two sub-districts in the second year (Year 2) and in two remaining sub-districts in third year (Year 3). The target population is children aged 3-59 months of age in the district of the Ouelessebouyou in Koulikoro region, in Mali.

In Year 1, the implementation of SMC will occur in four randomly selected sub-districts in Ouelessebouyou. Villages in these sub-districts will be randomized at 1:1 ratio to receive either a door-to door delivery (DDD) or fixed point distribution (FPD) of SMC. They will also be randomized to receive SMC as directly observed therapy (DOT) or non-directly observed therapy (NDOT). A census of the target population (children aged 3-59 months) will be carried out in all the selected villages prior to the intervention. During this census, blood samples will be collected in a randomly selected subset of study population to gather baseline data on cellular and humoral responses to malaria antigens, parasites prevalence and density on blood smears and frequency of the molecular markers of the resistance to SP and AQ at the start of the transmission season. The census list will be used to deliver the intervention and will be regularly updated. SMC will consist of the administration of full treatment course of sulfadoxine-pyrimethamine plus amodiaquine (SP+AQ) at monthly interval during the malaria transmission starting in August 2014. Children will be followed passively for the determination of the

incidence of the malaria disease (uncomplicated and severe malaria). A cross-sectional survey will be carried after the third round in November/December to determine the coverage of SMC, the prevalence of the malaria parasitemia and anemia as well as humoral and cellular immune responses in a randomly selected number of children. Data collected in year 1 will be analyzed to determine the optimal delivery method (DDD+ DOT or DDD+NDOT or FPD+ DOT or FPD + NDOT) based primarily on the coverage of SMC and secondarily on the incidence of clinical malaria. The difference in SMC coverage is expected to be reflected in the incidence of clinical malaria, and the latter will be used to support the data on coverage of SMC. [Should there be no statistically significant difference between the arms in coverage and incidence of the disease, the easiest method of the delivery will be recommended for Year 2.](#)

In Year 2, SMC will be implemented using the optimal delivery system (determined in Year 1) in two sub-districts assigned during Year 2 after a census of children under 5 years of age. Villages in these two newly selected sub-districts will be randomized to receive either three or four SMC rounds during the transmission season starting in August. Baseline data on malaria parasitemia, markers of resistance to SP and AQ and immune responses to malaria antigens will be collected at baseline prior to the intervention in these two sub districts through a cross-sectional survey. In order to assess the effect of the fourth dose of SP and AQ, children will be followed passively to measure incidence rate of clinical malaria, and a cross-sectional survey will be carried out at the end of the malaria transmission season in November/December in a randomly selected sample of children to determine the prevalence of malaria infection, anemia, and humoral and cellular immune responses. Children that participated in Year 1 will continue to receive three rounds of SMC in Year 2 using the best delivery method identified in Year 1. The choice of the optimal number of doses will be based on the incidence of clinical malaria between the two arms of children in the two newly selected districts. An absolute difference of 7.5 episodes per 100 children per year will be considered meaningful.

In Year 3, all study children in the eight selected sub-districts will receive SMC by optimal method and frequency determined in Year 1 and Year 2 and will be followed passively for clinical malaria episodes through the end of the season. Venous blood samples will be collected at the beginning (July/August) and the end of the transmission season (November/ December) in a subset of randomly selected children to assess humoral and cellular responses to malaria

antigens as well as the prevalence of malaria parasitemia among children who received SMC during one, two and three malaria transmission seasons. These outcomes will also be compared to those among children in the IMEP cohort who never received SMC, in a separate analysis taking into account the differences and similarities between the cohorts.

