## 5. Statistical Considerations and Data Analysis

### A. Sample Size and Power Calculation(s)

*Cross-sectional surveys.* Sample size for cross-sectional surveys will be based on the SMC coverage. Assuming 60% average coverage of SMC by the combination of nonoptimal methods (pools of two groups), 300 children/arm will be needed to detect 10% increase in average coverage for two pooled groups with at least 85% power correcting for multiple tests and using two Fisher's exact tests. To account for cluster sampling with a minimum 10 clusters per arm, interclass correlation of 0.01 (based on a previous trial showing vaccine coverage (Dicko et al BMC Pub Health 2011), and 5% missing data, 446 children will be surveyed per group (total of 1784 children).

*Passive surveillance.*

Assuming a clinical malaria attack rate of 0.3 per child per year in “3 rounds” arm, to detect an absolute difference in attack rate of the 0.075 episode/chil/ year (corresponding to 25% reduction) in the “4 rounds” arm, with a one sided p-value of 0.025 and power of 80%, using a quasi poisson model accounting for 20 equally sized clusters per arm with intraclass correlation of 0.01 and 5% missing data we will need 1386 per arm, or 2,772 subjects total.

*Immunological parameters.* We will base our sample size calculations for immunological endpoints on the humoral immune response to AMA1. We select this response because AMA1 is highly immunogenic from among malaria antigens. Also, the intervention in this trial is directed at reducing the blood stage burden of parasites during the malaria season, and the response to AMA1 reflects exposure to blood stage forms of the parasite. In earlier serology studies of young children participating in an AMA-1 vaccine trial in Bancoumana, Mali (Sagara et al, Vaccine, 2009), we observed the peak antibody titer against AMA1 to occur near the end of the malaria season (among children receiving control vaccine), with geometric mean antibody levels of 120 antibody units (95% CI, 70-205). Antibody levels just prior to the start of the malaria season (before vaccination) were 40 (25-75) antibody units. Based on these data, 467 subjects per

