### **B. Planned Interim Analyses (if applicable)**

At the end of the first transmission season, data will be analyzed to determine the optimal mode of delivery by comparing primarily the coverage of SMC and secondarily the incidence rate of the clinical malaria between the four intervention arms. In addition, descriptive analysis of the baseline frequencies of the immunological parameters, and molecular markers of the resistance of *P. falciparum* to SP and AQ, will also be performed at the end of Year 1.

Data collected in Year 2 will be used to determine the optimal frequency of the SMC rounds by comparing primarily the incidence of clinical malaria and secondarily the parasite prevalence at the end of season between the 2 arms. Descriptive analysis of immunological parameters and markers of drug resistance will also be performed.

Details of the statistical methods are provided below in the final analysis plan.

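### The Year 1 rule lets malaria incidence alone remove the easiest-method default, against its stated supportive role and with no error control across the two outcomes

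*Protocol*

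**What the plan says.** Section 4.A (Overall design) says that the Year 1 delivery mode is chosen "based primarily on the coverage of SMC and secondarily on the incidence of clinical malaria". It adds that a coverage difference should show up in incidence, and that "the latter will be used to support the data on coverage of SMC". The next sentence gives the fallback: "Should there be no statistically significant difference between the arms in coverage and incidence of the disease, the easiest method" is recommended for Year 2. The French text repeats the rule in section 4.2 (Schéma général), so it is not a slip of translation.

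Two other places give coverage the deciding role. The general description of the design in the Protocol Summary has the mode selected on Year 1 coverage and does not mention incidence. Section 3.B names coverage as the primary outcome for the mode of delivery, and reserves incidence as a primary outcome for the Year 2 question of three or four rounds.

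Section 5.B plans the end-of-Year-1 analysis as "comparing primarily the coverage of SMC and secondarily the incidence rate of the clinical malaria between the four intervention arms". Multiplicity is mentioned once, in the coverage sample size of section 5.A: "with at least 85% power correcting for multiple tests and using two Fisher's exact tests". Section 5.C compares incidence rates by generalized estimating equations and mentions no correction.

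**The concern.** The fallback sentence gives incidence a power that its supportive role does not. If the default holds only when neither outcome is significant, a chance incidence result with no coverage difference is enough to remove it. The decision then has two routes to a false positive, and only one carries a stated correction.

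The choice has long reach. The Year 1 mode is carried into the original four and the two new sub-districts in Year 2, into all eight in Year 3, and is meant to inform deployment across Mali. If the modes are truly equal, a false signal could lead to a harder method being adopted for no gain. The two outcomes could also point to different modes, and the rule does not say which prevails once the default has gone.

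**Working it through.** **The plan's own coverage figures (section 5.A).** Inputs: "Assuming 60% average coverage of SMC by the combination of nonoptimal methods"; "300 children/arm will be needed to detect 10% increase in average coverage for two pooled groups with at least 85% power"; at least 10 clusters per arm; intraclass correlation 0.01; 5% missing data. The 10% increase is read as 60% v 70%, with 600 children per pooled group. An overall two-sided alpha of 0.05 is assumed, so each of the two tests is at 0.025.

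- Clustered size: n = 300 × (1 − 0.01) / (1 − 300 × 0.01/10) = 297/0.7 = 424.3. Dividing by 0.95 gives 446.6. The plan's 446 reproduces.
- Power at 0.025 per test: null standard error √(2 × 0.65 × 0.35/600) = 0.02754; alternative standard error √((0.24 + 0.21)/600) = 0.02739; (0.10 − 2.241 × 0.02754)/0.02739 = 1.40, which gives 91.9%. Simulated Fisher's exact power is 90.3%. The stated 85% is met.

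**Chance that some significant result removes the default, all modes equal.** Coverage is held near 5%: 1 − 0.975² = 4.9%. If the outcomes are independent, P(either) = 1 − (1 − coverage error) × (1 − incidence error).

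- One global four-arm incidence test at 0.05: 1 − 0.9506 × 0.95 = 9.7%.
- Two pooled contrasts at 0.05 each: 1 − 0.975² × 0.95² = 14.2%.
- Three arms v DDD+NDOT at 0.05 each (incidence error 12.5% by simulation): 1 − 0.9508 × 0.8752 = 16.8%.
- Six pairwise tests at 0.05 each (incidence error 20.2% by simulation): 1 − 0.9508 × 0.7978 = 24.1%.

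A simulation of 1,000,000 draws of four equal arms allows for correlation between the outcomes:

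| Incidence tests | Correlation 0 | Correlation of size 0.8 |
|---|---|---|
| One global test | 9.6-9.7% | 8.3% |
| Two pooled contrasts, unadjusted | 14.2% | 11.8% |
| Three v DDD+NDOT, unadjusted | 16.8% | 14.3-15.2% |
| Six pairwise, unadjusted | 24% | 22% |
| Incidence corrected to 5% on its own (two contrasts) | 9.6% | 7.9% |
| Two contrasts × two outcomes, 0.0125 each | 4.9% | 4.1% |

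The first four rows cover the ways in which the text could be followed. The fifth shows that correcting each outcome separately is not enough. The last shows one alpha shared over both.

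**Chance of a false signal against the easiest method.** The figures above count significance in either direction. In the two-contrast model only half of each test's alpha counts against the easier level. With independent outcomes: 1 − (1 − 0.0125)² × (1 − 0.025)² = 1 − 0.9752 × 0.9506 = 7.3%. The rate is 6.8% at correlation 0.5 and 6.0% at 0.8. On coverage alone it is 1 − 0.9875² = 2.5%.

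**Coverage power if alpha is shared.** At 0.0125 per test: (0.10 − 2.498 × 0.02754)/0.02739 = 1.14, or about 87%. Simulated Fisher's exact power is 86.0%, still above the plan's 85%.

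**The case against.** The best defence is that the hierarchy is clear enough. The Summary selects on coverage, section 3.B makes coverage the primary outcome for mode, and sections 4.A and 5.B rank incidence second. A primary criterion with a secondary one that supports it is coherent. The fallback sentence says what happens when neither outcome differs; it does not say what happens when only incidence differs. If coverage decides, the error stays near 5%. One could even read the sentence so that the default falls only when both outcomes are significant, which gives 0.2-3.6%. The number of tests and the alpha for a secondary outcome also commonly belong in an analysis plan, which is not at hand.

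Much of this stands, and it limits what may be claimed:

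- A reader might infer that incidence alone then picks the mode. The protocol does not say so; it leaves that case open.
- A reader might take 12-17% as the trial's error rate. It rests on two or three unadjusted incidence tests. The two-test structure comes from the coverage sample size, and the three-test structure from a control arm named in the coverage paragraph. One global test fits the references to differences between the arms at least as well, and gives 8-10%.
- A reader might take 12-17% as the chance of adopting a harder method. It also counts results that favour the easiest one. With three comparisons against control, the directional figure depends on which arm is easiest, and the rule does not name it.

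The objection does not remove the conflict. As worded, the fallback sentence does not confine the decision to coverage. An analysis plan that follows it must still choose between two roles for incidence, and nothing in the protocol prevents that choice from being made after the Year 1 data are seen.

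**Conclusion.** The point holds as a fault in a stated decision rule. The fallback in section 4.A and its French counterpart, on its natural reading, lets either outcome remove the default. This contradicts the coverage-based selection in the Summary and section 3.B and the supportive role given to incidence in 4.A, and no error control spans the two outcomes.

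The size is conditional on two-sided 0.05, coverage held near 5% and the unstated incidence tests: about 8-10%, 12-17% or up to 24% for any significant result. The excess over 5% appears in every structure tried in which each outcome has its own 5% or more. The stronger inference, that the trial would choose a harder method 12-17% of the time, is not supported. Under equal modes, a wrong choice costs logistics rather than efficacy. The change should be made, but it is a correction to one rule.

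**What to change.** Amend the fallback sentence in section 4.A and in French section 4.2 to say that coverage alone decides whether the easiest-method default applies, in line with the Summary and section 3.B. Incidence is then reported as supportive, or tested only after coverage is significant.

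If the sponsor wants incidence to be able to displace the default by itself, the rule should say so and share one alpha over both outcomes. Examples are 0.0125 for each of two pooled contrasts on two outcomes, or Holm over those four tests. The 0.0125 split brings the joint error to 4.1-4.9% and keeps coverage power at about 86%. The rule should then also say which outcome prevails if they favour different modes.

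Either version needs a sentence or two in the rule, mirrored in the analysis plan, and no further data. The cost is that an incidence difference without a coverage difference no longer changes the mode, or needs a smaller p-value. The second option lowers incidence power, and section 5.A gives no Year 1 incidence power against which to judge the loss.

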#### ***Census and randomization***

Once community consent to the trial is obtained, a household census will be conducted and all households within the study areas with children under 5 years of age will be identified. At the time of census, a preliminary screening of potentially eligible children will be undertaken. Eligible children will be identified and written informed consent will be obtained from their caretakers for their inclusion in the trial. Children entered into the trial will be assigned a unique ID number and their demographic data (date of birth and/or age, and gender) will be collected.

The census will be updated at each SMC round and potentially eligible participants (such as children who did not reach the age of three months during the previous round) will be identified and screened for eligibility and enter into the study. This updated census will collect information on migration and death of children enrolled into the study for precise estimation of person-time of follow-up.

The unit of randomization will be village and all eligible children in a village will be allocated to the same study arm (DDD+ DOT or DDD+NDOT or FPD+ DOT or FPD + NDOT) to avoid confusion in Year 1. Villages in the selected sub-districts will be randomized at 1:1 ratio to receive either a door –to-door delivery (DDD) or fixed point distribution (FPD) of SMC. They will also be randomized to receive SMC as directly observed therapy (DOT) or a non-directly observed therapy (NDOT). In Year 2, villages in the two newly randomly selected districts will be randomized into two groups to receive either three or four rounds of SMC.

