### ***Inclusion and exclusion criteria***

Children of either sex aged 3-59 months of age at the start of each period of drug administration will be eligible for inclusion in the trial, provided that parental consent is obtained. Children under the age of three months on the date of the start of drug administration will be excluded that year, as SMC is not recommended for children in this age group whose risk of acquiring malaria is low. Children who reach the age of 59 months or more at the end of the first or second years of treatment will not receive SMC in subsequent years. Exclusion criteria will be as limited as possible to make the results of the trial broadly applicable and will include i) a severe, chronic illness, ii) a known allergy to one of the study drugs, iii) known HIV positive subjects using Cotrimoxazole. [Children with acute clinical malaria at the time of SMC drug administration will be treated by ACT and will not be given SMC drugs during that round as per WHO recommendation. They will receive SMC drugs during subsequent cycles.](#)

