group will provide 80% power, to detect a 2 fold or greater reduction in peak AMA1 antibody levels among the children receiving SMC, accounting for cluster sampling in 10 equally sized clusters with 0.01 intraclass correlation as well as 10% missing data given that samples may be inadequate or spoil during routine collection and transport.

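### The Year 3 immune comparison by one, two and three SMC seasons sets no age band for its sample, so seasons received is tied to age and the size of the three-season group is left open.

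*Protocol*

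**What the plan says.** Protocol section 4.A (Overall design) starts SMC in four sub-districts in Year 1, two more in Year 2 and the last two in Year 3, with treatment "at monthly interval during the malaria transmission starting in August 2014". In Year 3 all eight sub-districts receive SMC. Blood is then taken "in a subset of randomly selected children to assess humoral and cellular responses to malaria" antigens, as well as "prevalence of malaria parasitemia among children who received SMC during one, two and three malaria transmission seasons". No age limit, stratum or quota is attached to the draw. The section on follow-up and measurement of outcomes likewise describes each year's survey only as a random sample of children.

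The age rules are in the inclusion and exclusion criteria: "Children of either sex aged 3-59 months of age at the start of each period of drug administration will be eligible", and "Children under the age of three months on the date of the start of drug administration will be excluded that year". The census section differs. It updates the list at every round and screens new entrants "such as children who did not reach the age of three months during the previous round".

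Section 5.A states that 467 subjects per "group will provide 80% power, to detect a 2 fold or greater reduction in peak AMA1 antibody levels" among children receiving SMC, allowing for 10 clusters, an intraclass correlation of 0.01 and 10% missing data. It does not define the groups. Section 5.C exempts the immune endpoints from intention-to-treat and analyses them by the number of SMC treatments received.

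**The concern.** The number of seasons a child can have received depends on two things: the year its sub-district started, which is randomised, and the child's age, which is not. Analysis by seasons received brings age into the comparison. In the Year 1 sub-districts the split is complete: three-season children are the oldest and one-season children the youngest. Only the later-starting sub-districts supply older children with fewer seasons.

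The protocol itself says that responses to AMA1 and MSP1 reflect exposure to blood-stage parasites. Older children have had more time to be exposed, including time before SMC began. A three-season group that is older could therefore show higher antibody levels for reasons unrelated to SMC, and this could mask the reduction the trial is looking for. The documents do not allow the size of that bias to be estimated. Age adjustment helps where exposures overlap in age. It cannot help where only one exposure exists.

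At stake is the stated aim of learning what one, two and three years of SMC do to immunity. Who is bled is settled in the field, and children who were not sampled cannot be added later.

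**Working it through.** **Inputs.** First season August 2014 and Year 3 season August 2016 (section 4.A); ages 3-59 months (inclusion criteria); 467 per group, 80% power, 2-fold change, 10 clusters, ICC 0.01, 10% missing (section 5.A). Assumptions not in the documents: uniform ages over 57 monthly bands, equal draws per start-year group, two-sided alpha of 0.05.

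**1. Age floors in August 2016.** Three seasons: 3 + 24 = 27 months. Two seasons: 3 + 12 = 15 months. If entry at later rounds is allowed, as the census section implies, each floor falls by about two months, to about 25 and 13.

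**2. Mix by start year.** The bands are 3-14 months (12), 15-26 (12) and 27-59 (33).

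| Sub-districts starting in | Three seasons | Two seasons | One season |
|---|---|---|---|
| Year 1 | 33/57 = 58% | 12/57 = 21% | 12/57 = 21% |
| Year 2 | none | 45/57 = 79% | 12/57 = 21% |
| Year 3 | none | none | 100% |

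The 58% becomes 61% with a 25-month floor, and 53-57% if numbers fall by 2-8% per year of age.

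**3. Mean ages by seasons received** (band midpoints, weighted by band width).
- Three: (27 + 60)/2 = 43.5 months.
- Two: (12 × 21 + 45 × 37.5)/57 = 34.0 months.
- One: (12 × 9 + 12 × 9 + 57 × 31.5)/81 = 24.8 months.

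Below 27 months there are no three-season children. Below 15 months there are only one-season children.

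**4. The plan's 467.** 467 × 0.9 = 420.3 analysable, or 42.03 per cluster. Design effect 1 + 41.03 × 0.01 = 1.410, so effective n = 420.3/1.410 = 298. For 80% power at ln 2 = 0.693:

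SD = 0.693/(1.960 + 0.842) × √(298/2) = 3.02 on the natural-log scale.

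The 95% CI of 70-205 gives a standard error of ln(205/70)/3.92 = 0.274. An SD of 3.02 therefore needs about (3.02/0.274)² ≈ 121 children behind that interval. The protocol does not give that number, so 467 is attainable but cannot be independently reproduced.

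**5. If 467 were drawn per start-year group from all ages.**
- Three seasons: 467 × 33/57 = 270 drawn, 243 after loss. Effective n in 10 clusters = 243/(1 + 23.3 × 0.01) = 197.
- One season: 467 × 81/57 = 664 drawn, 597 after loss. Effective n = 597/1.587 = 376 in 10 clusters, or 597/1.189 = 502 if spread over 30.
- SE = 3.02 × √(1/197 + 1/376) = 0.265, power 74%. With 30 clusters, SE = 0.254, power 78%.

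These figures ignore the age difference. Restricting the same draw to the age band that all groups share leaves about 270 drawn from each start-year group (effective n 197 each). SE = 3.02 × √(2/197) = 0.304, power about 63%.

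**The case against.** The best defence is that the protocol promises no more than it can deliver. Section 5.A sizes a comparison of children who receive SMC with those who do not, matching the second specific objective. It never assigns 467 to a three-season group. The Year 3 sentence can be read as random selection within groups defined by seasons received. Nothing says that only 467 children come from the Year 1 sub-districts: the Year 1 coverage survey alone is 1,784 children, and a survey of that size repeated there would give about 1,784 × 33/57 = 1,033 three-season children. Quotas may also sit in a SAP or operating procedure that is not shown.

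Most of this stands as regards numbers. A reader might infer that the three-season group misses a stated target by 42%, but there is no such target. A reader might also infer that power drops to 60-70% because start-year groups are diluted. Section 5.C rules that out by analysing immune endpoints by treatments received. Setting 270 against one full group of 467 would give about 71%, but that understates the comparator, since the one-season group would be about 597 after loss.

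The defence does not remove the age problem. Selection within season groups would fill the counts, yet every three-season child would still be at least 27 months old (or about 25), while the other groups would include younger children. No passage provides an age limit or matching.

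**Conclusion.** The concern holds in a limited form. As written, the Year 3 immune sample makes seasons received structurally dependent on age, with mean ages of about 25, 34 and 43.5 months under uniform ages and equal draws. There is no overlap with the three-season group below 27 months. This follows from the protocol's own dates and age rules; only the exact means rest on assumptions.

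The shortfall in numbers is conditional. It arises only if about 467 children are drawn without stratification in the Year 1 sub-districts. About 270 (roughly 250-290) would then have three seasons, with power of about 74-78% instead of 80%. That power also rests on an SD of 3.02 recovered from the plan's own figure and on an assumed two-sided 0.05. The 58% counts age eligibility only, so missed seasons or in-migration would lower it.

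Two points in the text need settling: which groups the 467 covers, and whether a child who turns three months old during a season may enter that year. On the second, the inclusion criteria and the census section disagree and must be reconciled.

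**What to change.** In section 4.A (Year 3) and section 5.A, state that the 467 per group for the comparison by seasons received is drawn, in all three start-year groups and for the IMEP comparison, from children old enough to have been eligible in August 2014. That is 27-59 months in August 2016, or whatever floor results once the two entry rules are reconciled. Name the groups that the 467 covers. Keep the 3-59 month random sample for parasite prevalence and anaemia.

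Start-year group then matches seasons of eligibility, and all groups share one age band.

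**Cost.** One or two sentences, and no increase in the 467 per group. Supply looks ample: if the Year 1 sub-districts hold half of the 10,800 children (an assumption), about 5,400 × 33/57 = 3,126 meet the floor. Filling the group from an all-age draw would instead take about 467 × 57/33 = 807 children. Children of the right age in the survey sample can serve both purposes, but some may have to be added from the census list. The documents do not show how many IMEP children will be in this age band, so that needs checking. The main downside is that the comparison by seasons says nothing about children below the floor; any results for them would be descriptive.
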